### Harms

As this is an evaluation of the FEAST program, it is not anticipated to produce adverse reactions/events. To date, no issues have been reported from the 170 schools that have implemented FEAST between 2018 and 2020. To our knowledge, there are no known published studies in school-based nutrition experiential interventions reporting adverse reactions/events. However, this study has included four questions in the teacher evaluation to assess ‘harms’. The survey includes questions that ask teachers whether: they completed the mandatory FEAST Program risk assessment prior to delivering the program to their students (Refer to Additional file 4 for description of risk assessment components); whether any students were harmed; if they were harmed, how many were harmed and what types of harms occurred in the classroom setting over the course of the FEAST Program. (Refer to Additional file 7 for full details of questions and response options on harms in the teacher surveys.)

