OzHarvest provides training, resources and support to teachers to deliver a recommended 1.5-h lesson/week, for a 10-week unit of inquiry (incorporating 10 theory and six practical activities) within the classroom setting. The FEAST program has been integrated with lessons mapped to the Australian Curriculum, embracing Grade 5–6 key learning areas (KLAs) i.e. English [44]; STEM (Science, Technology, Engineering, and Mathematics) curriculum [45]; general capabilities (Literacy, Numeracy, Information and Communication Technologies, Critical and Creative Thinking, Personal and Social Capability and Intercultural Understanding) [46]; and the cross-curriculum priority of sustainability [47]. FEAST has been aligned with the Australian Dietary Guidelines and state/territory-based healthy eating strategies [1], with all recipes including either fruits and/or vegetables (which are also the two most wasted food groups [48]). The program includes a range of educational resources designed to assist in the delivery of the theory and practical components as outlined in Additional file 2 [49]. The lesson plan topics are outlined in Additional file 3 and the practical guide components are outlined in Additional file 4.

Grade 5–6 classroom teachers from the schools that volunteer to participate in the FEAST program, will be invited for a training workshop at OzHarvest offices. A Professional Learning Program will be delivered over six hours of face-to-face training. During the training day, two FEAST education team members will train the teachers in food preparation and cooking skills (making the hot and cold recipes designed for the FEAST program). To assist the teachers and students during the class practical components, teachers will be provided with instructions and resources to seek volunteers throughout the school community such as parents/caregivers, grandparents, and/or school staff etc. Trained volunteers will also be available through OzHarvest, to assist during the practical components. It is recommended that the teachers organize at least one adult per five students, for each of the practical sessions, in addition to themselves.

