A 3-h NESA accredited online teacher training version of the FEAST program was developed for schools in regional and remote areas of NSW (as defined in the *‘school facts location identified’*), which is published on the *MySchool* website [50]. This can also be used by teachers that are unable to attend the 6-h face-to-face training, due to additional circumstances, including COVID19 restrictions.

The teachers using the online training have the option to work through the training module at their own pace. Teacher instructions on how to use the online learning resources and adapt them to their students’ needs have also been included in the online training module. Lesson plans; how to conduct the practical cooking sessions with instructional videos on good cooking techniques for making some of the recipes at home, including parent roles; and access to all of the same resources as the face-to-face training are available through the online module. Email and phone support from the FEAST education team will also be available to the teachers undertaking the online training. The online training will also be used in the event that COVID19 restrictions prevent face-to-face training in 2021.

Strategies to improve adherence to the FEAST program include: accredited teacher training program; a complete curriculum package for the teachers; lessons plans mapped to the Australian Curriculum, KLAs (English and STEM), general capabilities, and cross-curriculum priority area of sustainability; activity booklets for students with answer booklets for teachers; training of OzHarvest volunteers to assist in the practical activities (subject to COVID19 regulations); as well as open communication (phone and/or email) between the FEAST education team and teachers during implementation, to provide support.

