##### Cooking (skills, self-efficacy and behaviour)

The proportion (%) of students reporting the following, will be calculated: the ability to prepare food (i.e. fruit snack, vegetable snack, salad); help family make a meal; measure ingredients; cut food; follow a recipe; and the number of times/week they help their family cook dinner at home. Also, the mean score of the number of ‘yes’ responses to these questions will be calculated out of a possible seven ‘yes’ responses, and compared between baseline and post-intervention. The seven questions to assess these outcomes were taken from the survey used in the *Cooking with Kids* program and have been validity-tested for self-efficacy among children aged 9–11 years [57]. The question that measures behaviour change (i.e. help their family cook dinner at home), was taken from the *Experiential Cooking and Nutrition Education Program*, that was designed to increase cooking self-efficacy and vegetable consumption in children in Grades 3–8 [58] however, it has not been tested for validity and/or reliability.

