##### Program satisfaction (teacher and student)

To assess satisfaction, the teachers will be asked: if they felt the training was effective and whether it helped prepare them to deliver the program within the classroom setting; to rate the effectiveness of the resources provided; whether the program met Grade 5–6 KLAs, aligned with the cross-curricular priority of sustainability and general capabilities and whether it was easy to implement STEM lessons; whether it met their student’s learning needs; and whether it was easy to integrate the program into the classroom routine. Teachers will also be asked whether they thought their students found the activities and website easy to follow and resources engaging.

To assess satisfaction, students will be asked whether: FEAST activities and website were easy to read and understand; if they thought the program was fun; if they enjoyed cooking; if they cooked some of the classroom recipes at home; whether they learnt anything new about food preparation and cooking; and whether they created a cookbook and if so, if they enjoyed creating it. Both student and teacher post-FEAST surveys ask them to rate how likely they would recommend the FEAST program to others.

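### Harms are sought only from teachers, in wording centred on the classroom, so injuries while making FEAST recipes at home are not systematically captured

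*Protocol article*

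**What the plan says.** The Harms section expects no adverse events and notes that no issues have been reported from the 170 schools that have run the program. It then states that "this study has included four questions in the teacher evaluation to assess" harms. One of the four asks whether the mandatory risk assessment was completed. The rest are described as "whether any students were harmed; if they were harmed, how many were harmed and what types of harms occurred in the classroom setting"; the last of them asks, in full, "what types of harms occurred in the classroom setting over the course of the FEAST Program". For the exact items the reader is told: "Refer to Additional file 7 for full details of questions and response options on harms in the teacher surveys". That file is not among the documents at hand.

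The Intervention section places the scheduled teaching at school, "for a 10-week unit of inquiry (incorporating 10 theory and six practical activities) within the classroom setting". The same section lists, among the contents of the online teacher-training module, "instructional videos on good cooking techniques for making some of the recipes at home, including parent roles".

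Two questions to the children concern cooking at home. Under program satisfaction, students are asked "if they cooked some of the classroom recipes at home". Among the secondary cooking outcomes is "the number of times/week they help their family cook dinner at home", which the article treats as its measure of behaviour change.

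**The concern.** The trial looks for cooking at home by asking the children, but it looks for harm by asking teachers, in language tied to the classroom. Teachers would not normally see an injury in a child's kitchen. The participants are 10 to 12 years old, and the program teaches them food preparation with hot and cold recipes, so a minor cut or burn is foreseeable wherever a recipe is made.

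What is at stake is how far the safety statement reaches. The sponsor expects no adverse events, and this trial is a chance to check that expectation prospectively. If teachers report none, readers are likely to take the result as covering the whole program, including recipes repeated at home. The more the program succeeds in moving cooking into the home, the more of the cooking falls outside what teachers can observe.

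**Working it through.** The plan gives no figure to reproduce, and no calculation applies. The check sets the relevant sections side by side.

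1. **Who is asked about harm.** Only teachers (Harms section). Of the four questions, one concerns the risk assessment, which leaves 4 − 1 = 3 on actual harm. The section mentions no student or parent question and no other reporting route.
2. **Which place is named.** Only the classroom. As the sentence is written, the phrase directly follows the question on types of harm. The questions on whether anyone was harmed and how many carry no place limit of their own.
3. **Where cooking takes place.** The six scheduled practical activities are in the classroom (Intervention section). Making some recipes at home is supported by material in the online module. That module was developed for regional and remote schools, is open to teachers who cannot attend in person, and will be used if COVID19 restrictions prevent face-to-face training.
4. **Who is asked about cooking at home.** The children, by two different questions. One is specific to FEAST: whether classroom recipes were made at home (program satisfaction). The other is general: how often the child helps to cook dinner (secondary outcome).
5. **Comparison.**

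| Setting | Is the cooking asked about? | Is harm asked about? |
|---|---|---|
| Classroom practical sessions | Yes, of teachers and students | Yes, of teachers, who are present |
| FEAST recipes made at home | Yes, of students | Not specifically; only through a teacher who happens to be told |

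The second row is the gap. A home injury is not barred from the record, but nothing in the described plan goes looking for it.

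**The case against.** The strongest case on the other side is that the plan asks about harm where the program is delivered. FEAST is described as classroom-based, no home session is scheduled, a risk assessment is mandatory, and no issues have been reported so far. Asking children as well would then be a preference and not the repair of an error. Much of this stands: nothing here is a contradiction, and the effectiveness analysis is untouched. The reporting record, however, does not settle the matter. The article does not say how those reports were gathered, so they may share the same limitation.

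Several stronger readings are tempting, and the article does not support them:

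- **That home injuries cannot be recorded, or that their capture is zero by definition.** Two of the three questions on actual harm have no explicit place limit, and the exact items are in Additional file 7, which is not shown. A teacher told of a burn at home could answer yes.
- **That home cooking is a required part of the intervention.** It is supported and asked about, but it is not scheduled. The COVID19 fallback concerns teacher training; the article does not say that the children's practical sessions move to the home.
- **That every injury while cooking at home is a program harm.** The dinner question is not about FEAST recipes, and children may help with dinner whether or not they have had the program. Only the question on classroom recipes ties home cooking to FEAST.
- **That a number of missed events can be given.** If one assumes 500 intervention children (10 schools × 50) and that 30–60% repeat a recipe at home, then 0.30 × 500 = 150 to 0.60 × 500 = 300 children would have cooked at home. Both inputs are assumptions, and the result counts children exposed, not children hurt.

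**Conclusion.** The point holds in a limited form. As described, harms are sought only through teachers, in wording centred on the classroom, while the materials support making recipes at home and the children are asked about doing so. Injuries while making FEAST recipes at home are therefore not systematically captured, and a report of no harm would speak mainly to what teachers saw or were told.

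The size is unknown, since the article gives neither the frequency of home cooking nor an event rate. The conclusion assumes that the Harms section fairly describes the instruments, and in particular that the student surveys, which are also not shown, contain no harms question. Severity is low: the primary outcomes, power and type I error do not depend on this.

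**What to change.** - **Teacher survey:** word the harms items so that they are not limited to the classroom. If Additional file 7 already does this, only the description in the article needs to change.
- **Student post-program survey:** next to the existing question on making classroom recipes at home, add one item asking whether the child was hurt while making a FEAST recipe, and whether this was at school or at home.
- **Reporting:** give school and home counts separately and descriptively. The existing question on home recipes supplies a natural denominator for the home count. Because the item concerns FEAST recipes, it offers no comparison with the wait-list schools.
- **If the student item is not added:** limit any harms conclusion to classroom events known to teachers.

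The cost is a wording edit and one short item in a REDCap survey that already exists, with negligible extra completion time. The downside is that children's reports are unverified and likely to be mostly minor, so they should not be read as confirmed events.

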## Discussion

The implementation of the FEAST program by OzHarvest, across primary schools in NSW, provides an invaluable opportunity to gain scholarly and translational research outcomes. As such, this paper has described the protocol for a pragmatic, non-randomized controlled trial involving a wait-list control group. The evaluation of FEAST will contribute to a growing body of work investigating the effectiveness of school-based interventions incorporating nutrition and sustainability education with experiential activities.

There are both strengths and limitations to the evaluation design. It has been acknowledged that using a non-randomized design has the potential to introduce selection bias [79]. However, due to the pragmatic nature of this study, which will be conducted in the real world, where schools will self-select to participate in both the FEAST program and subsequently in the trial, randomization will not be possible. Despite this potential for bias, using a wait-list control with pre- and post-measures, should help mitigate some of the issues related to this type of bias. Other protections from potential bias when using a NRCT design include the provisions of a detailed protocol with pre-specified statistical analysis plan which, should include, predefined primary and secondary outcomes, their derivations from measured variables, methods for managing missing data, as well as planned subgroup and sensitivity analyses [83], all of which, have been included in this protocol description.

Another limitation of this study is the reliance on self-reported measures from children aged 10–12 years. However, the majority of questions utilised to create the FEAST survey instrument, were taken from reliable and validated surveys that have been tested among this age group [54, 56, 57, 65]. Furthermore, it has been found that cognitive abilities required to self-report food intake increase among children aged 8 years and over [84], and the FEAST program is designed for children over this age. Another concern with self-reported measures, is that there is the possibility that students may answer in a socially desirable manner and as a result they may be over- or underestimating their responses, depending on recall bias. Although this is a common challenge with this type of research, to limit the potential for social desirability bias, the students will be advised prior to survey completion that the survey is not a test, there are no ‘right’ or ‘wrong’ answers, and that it is important for them to report as honestly as possible [85].

Strengths of the FEAST program include the incorporation of a number of components that have shown to contribute to effective school-based nutrition education programs for children, such as the implementation of: multi-component strategies (involving teachers, parents/caregivers and community) [86]; age-appropriate, hands-on experiential activities (such as food preparation and cooking) [86]; exposure to F&V [86]; strategies to enhance fidelity by training the implementers with standardized protocols (i.e. accredited teacher training) [86]; integration of such programs within the curriculum (aligned with the Grades 5–6 key learning areas in the Australian Curriculum) [19]; as well as proper alignment between the objectives, intervention, and desired outcomes [86].

The strengths of the evaluation design include the use of: the 33-item SPIRIT checklist to guide the design of the protocol; using a controlled design; questions for the primary outcomes derived from reliable and validated measures tested on this age group; many of the secondary outcomes, were also derived from reliable and validated measures. The trial is well powered to detect changes in outcomes and the trial statistician will be blinded to group allocation when conducting the statistical analyses. Also, this trial has included qualitative questions embedded within the quantitative surveys. The combination of qualitative and quantitative components within the surveys, will enable the trial’s conclusions to be expanded upon [87, 88]. If triangulation of results is found between qualitative and quantitative components, then convergence of outcomes allows for stronger inferences about findings [87, 88].

Furthermore, non-randomized evaluation designs can contribute data on the effectiveness of interventions, and if conducted and reported systematically, have the capacity to contribute to building evidence-based public health practices [89]. Accordingly, the TREND (Transparent Reporting of Evaluations with Nonrandomized Designs) [89] and the CONSORT (Consolidated Standards of Reporting Trials) statement for pragmatic trials [90] will be used to report outcomes.

Given the challenges of promoting healthy diets, sustainable eating and reducing food waste at the population level, the FEAST program is well-positioned to play a key role in this school-based approach to engage students to eat healthily and sustainably. Initiatives undertaken within the school system have the added advantage of reaching large, diverse populations, placing them in a unique situation to deliver universal and equitable public health strategies [11, 23, 33].

If this program demonstrates effectiveness, FEAST will have the potential to benefit students by providing them with a set of tools to help them achieve healthy and sustainable eating practices. FEAST also has the potential to support the Australian Curriculum with health promoting and sustainability messages, which could contribute to: health promotion within schools [91]; sustainable schools initiatives [92]; government-supported public health initiatives [4, 93–96]; prevention of chronic conditions, in the long term [97, 98]; the national agenda to reduce food waste [36] as well as to the sustainable development goal targets for 2030 [92, 99, 100].

## Data Availability

Data not applicable for a protocol. Other than information published in this protocol, FEAST training materials remain the property of OzHarvest.

## Abbreviations

NCDs: Non-Communicable Diseases
F&V: Fruits and Vegetables
FEAST: *Food Education and Sustainability Training*
PPM: Precede-Proceed Planning Model
SCT: Social Cognitive Theory
NSW: New South Wales
SPIRIT: Standard Protocol Items for Clinical Trials
NRCT: Non-randomized Controlled Trial
KLAs: Key Learning Areas
STEM: Science, Technology, Engineering, and Mathematics
PI: Primary Investigator
ICSEA: Index of Community Socio-Educational Advantage
CI: Confidence Intervals
T1: Timepoint 1
T2: Timepoint 2
T3: Timepoint 3
SD: Standard Deviation
FFQ: Food Frequency Questionnaire
MCNQ: Modified Child Nutrition Questionnaire
CALD: Culturally and Linguistically Diverse
GLMMs: Generalised Linear Mixed Models
ICC: Intracluster correlation coefficients
ITT: Intention-To-Treat Analysis
TREND: Transparent Reporting of Evaluations with Nonrandomized Designs
CONSORT: Consolidated Standards of Reporting Trials
